### Stigma Behaviours and attitudes towards mental health

***Reported and Intended Behaviour Scale (RIBS)*** is used to assess reported and intended behavioural discrimination among the general public against people with mental health problems. The RIBS consist in 8 items; the first four items of the RIBS are designed to assess prevalence (past and current) of behaviour in each of the four contexts (1. living with; 2. working with; 3. living nearby; and 4.being in a relationship with someone with a mental health problem) while items 5–8 ask about intended (future) behaviour within the same contexts [34, 35]. For the purposes of this study, we selected four items from 5 to 8. It uses an ordinal Likert scale with five response options: “totally agree”, “somewhat agree”, “neither agree nor disagree”, “somewhat disagree”, “strongly disagree” from 5 to 1 points, respectively. The total score is obtained from a sum of the total answers ranging from 4 to 20. Higher scores indicate greater agreement with engaging the stated behaviour. The Spanish version will be used in this study.

***The Scaling Community Attitudes toward the Mentally Ill (CAMI)*** is an instrument for the systematic description of the attitudes of the community towards mentally ill people [36], which consists of 40 items divided into four dimensions (Authoritarianism; Benevolence; Community mental health ideology and Social restrictiveness). Only the “Authoritarianism” 10-item dimension in the Spanish version will be used [37]. Five of the 10 items are expressed as positive and five as negative. The score for each subscale is the sum of the positive items, and the reverse of the negative items. All items are scored on an ordinal scale (5–1), respectively, ranging from 10 to 50 for each factor. Higher scores mean greater agreement with engaging in the stated attitude.

### Others outcomes

The secondary outcome of the study is the acceptability of intervention, to measure the degree of receptivity by the students towards the proposed interventions. Other outcomes of the study are the mental health symptoms and emotional wellbeing, intention to change about a mental health problem, bullying and cyber-bullying behaviours, health-related quality of life (HRQoL), help-seeking behaviours and use of treatment.

**Acceptability and satisfaction of interventions:** these variables will be assessed by a short questionnaire specially developed for this study. It consists of six items which integrate the following dimensions: 1) interesting; 2) useful; 3) practical; 4) duration; 5) resolution of doubts and 6) activity recommendations. In addition, we will use one open question to express possible proposals, claims and/or comments.

### Mental health symptoms and emotional well-being

***Strengths and Difficulties Scale (SDQ)*** (Spanish version) [38–40]. The SDQ consists of 24 items which generate scores along five subscales: emotional symptoms, conduct problems, hyperactivity-inattention, peer problems, and prosocial behaviour (positive mental health). Each item is rated 0, 1 or 2 points in accordance with being “absolutely true”, “somewhat true” or “not true”. The score is inverted in those items whose presence indicates positive features. The total score ranges from 0 to 50. It is suggested that individuals with scores above the cut-off (depending on each study population) should be evaluated more closely due to the increased risk of any alteration in mental health. The SDQ has been validated for use with adolescents aged 11–16 with a Cronbach’s alpha of 0.82 for the total difficulties scale [40, 41].

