A secondary hypothesis to be tested will be: participation in the intervention groups (SP, MHL and MHL + SR) will reduce mental health symptoms, increase emotional well-being and help-seeking behaviours, reduce bullying and cyberbullying at school, and improve HRQoL immediately after 2 weeks, 6 months and 12 months post-intervention, compared to a waiting list control group.

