### Measures

The variables and instruments selected, as well as the evaluation programme timeline, are detailed in Table 3. Collected data will then be imported using a teleform format program onto a computer database.

**Table 3 Tab3:** Outcome measures

Outcome measures	Timeline			
	Pre-intervention	Post-intervention		
		2 w	6 mo	12 mo
Primary outcomes				
1. Mental Health Knowledge				
EspaiJove.net Mental Health Literacy Questionnaire (EMHLQ)	X	X	X	X
2. Behaviour and Attitudes Towards Mental Health (Stigma)				
Reported and Intended Behaviour Scale (RIBS)	X	X	X	X
The Scaling Community Attitudes toward the Mentally III (CAMI) - Authoritarianism subscale	X	X	X	X
Others outcomes				
3. Acceptability and satisfaction				
Satisfaction questionnaire		X		
4. Mental Health Symptoms and Emotional Well-Being				
Strengths and Difficulties Questionnaire (SDQ)	X	X	X	X
5. Bullying and Cyber-Bullying Behaviours				
Bullying and Cyber-Bullying Questionnaire	X	X	X	X
6. Intentions to Change				
Intentions to Change Questionnaire (ICQ)	X	X	X	X
7. Health-related quality of life				
EuroQol Questionnaire (EQ-5D-5 L)	X	X	X	X
8. Help-seeking				
General Help-Seeking Questionnaire (GHSQ)	X		X	X
9. Use of Health Services and Treatment				
Use of Health Services and Treatment questionnaire	X		X	X
10. Health Benefits Questionnaire				
Familiar, academic and general health questions	X		X	X

*Abbreviations*: *mo* months, *w* weeks

First of all, socio-demographic variables will be collected: age; date of birth; gender; nationality; city/village; neighbourhood of residence or postcode. The following variables are listed below:

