### Help-seeking and use of treatment

The instrument selected consists of two parts: (i) the first question asks whether the person has received psychological and/or medicinal treatment for an MH problem at any time in her/his life; and (ii) the second part includes the first item from the Spanish version of the ***General Help-Seeking Questionnaire (GHSQ)*** for measuring help-seeking behaviour in adolescents [46, 47]. The GHSQ asks participants to respond to each problem-type by rating their help-seeking intentions on a 7-point scale ranging from 1 (“extremely unlikely”) to 7 (“extremely likely”) for each help source option including “no one.” The sum of the points gives a total score ranging from 5 to 35. Higher scores indicate higher help-seeking intentions. Additionally, we added an econometric questionnaire of 8 items on the use of services for the purpose of the cost-effectiveness study.

**Health Benefits Questionnaire:** 17-item questionnaire to include information about: a) family: parental age, studies and occupation; number of brothers/sisters and their ages; b) academic scope: years in the same school, repeated school years, average grade, number of failed subjects and number of written warnings; and c) health: difficulty sleeping and general state of health.

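### As printed, the SDQ coding runs opposite to its stated reading and range, the GHSQ sum leaves the 'no one' rating unresolved, and help-seeking is hypothesised at 2 weeks but not measured then

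*Protocol article*

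**What the plan says.** **SDQ** (Protocol article, *Mental health symptoms and emotional well-being*). The article gives five elements of the scoring:
- Item count: "The SDQ consists of 24 items which generate scores along five subscales".
- Item coding: "Each item is rated 0, 1 or 2 points in accordance with being “absolutely true”, “somewhat true” or “not true".
- Reversal: "The score is inverted in those items whose presence indicates positive features".
- Range and direction: "The total score ranges from 0 to 50. It is suggested that individuals with scores above the cut-off" deserve closer evaluation because their risk is raised.

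**GHSQ** (*Help-seeking and use of treatment*). Pupils say how likely they are to turn to each option, with 1 as the lowest rating and 7 as the highest. The article describes the rating and the total in these words: "for each help source option including “no one.” The sum of the points gives a total score ranging from 5 to 35". A higher total is said to mean stronger intention to seek help. No reversal or exclusion of 'no one' is mentioned.

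**Timing.** The secondary hypothesis (end of *Background*) is that the programmes will reduce symptoms and also "increase emotional well-being and help-seeking behaviours, reduce bullying and cyberbullying at school, and improve HRQoL immediately after 2 weeks", as well as at 6 and 12 months. Table 3 (*Measures*) marks the GHSQ before the intervention and at 6 and 12 months, with no entry at 2 weeks.

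**The concern.** A scoring description has to settle three things: which way the total runs, what values it can take, and when it is measured. The text contradicts itself on the first two for the SDQ, leaves the direction of one component open for the GHSQ, and contradicts itself on the third for help-seeking.

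Both scales carry directional secondary hypotheses: symptoms should fall and help-seeking should rise. If the SDQ were scored by the printed rule and read by the printed interpretation, a benefit would be reported as harm. If 'no one' were added unreversed, a real gain in help-seeking would be diluted, because one component moves against the rest. The 2-week part of the help-seeking hypothesis would have no GHSQ data behind it.

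**Working it through.** **1. SDQ direction.** Let *p* of the 24 items be positively worded and 24 − *p* describe symptoms.
- Symptom item as printed: absolutely true = 0, somewhat true = 1, not true = 2.
- Positive item after inversion (2 − printed value): absolutely true = 2, somewhat true = 1, not true = 0.
- Worst profile (every symptom absolutely true, every strength not true): (24 − *p*) × 0 + *p* × 0 = 0.
- Best profile (no symptom true, every strength absolutely true): (24 − *p*) × 2 + *p* × 2 = 48.

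*p* cancels, so the result does not depend on how many items are positive. A higher total means better mental health, the opposite of the cut-off sentence. Inverting the positive items does not repair this; it makes every item run the same wrong way. One symptom moving from absolutely true to not true raises the total by 2.

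With the anchors the other way round (not true = 0, absolutely true = 2, positive items inverted), the worst profile scores 48 and the best 0, which agrees with the cut-off sentence.

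**2. SDQ range.** The stated range is 0 to 50. From the stated inputs, 24 × 2 = 48, so the figure does not reproduce. A maximum of 50 needs 25 items (25 × 2 = 50).

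**3. GHSQ range and direction.** With *k* summed ratings the range is *k* to 7*k*. *k* = 5 gives 5 to 35, which reproduces the stated range; *k* = 4 gives 4 to 28 and *k* = 6 gives 6 to 42. So five ratings are summed. The article does not list the options, which leaves these possibilities:

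| How 'no one' enters | Strongest help-seeker | Weakest help-seeker | Spread |
|---|---|---|---|
| One of the five, unreversed | 4 × 7 + 1 = 29 | 4 × 1 + 7 = 11 | 18 |
| One of the five, reversed (8 − rating) | 4 × 7 + 7 = 35 | 4 × 1 + 1 = 5 | 30 |
| Rated but not summed, five real sources | 5 × 7 = 35 | 5 × 1 = 5 | 30 |

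On the first row, a total of 35 can be reached only by a pupil who is extremely likely to turn to no one. As an extreme illustration, take a pupil whose 'no one' rating goes from 7 to 1 while one real source goes from 1 to 7:
- unreversed: (1 − 7) + (7 − 1) = 0
- reversed: (7 − 1) + (7 − 1) = +12
- 'no one' left out: +6

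**4. Timing.** In Table 3 the SDQ, bullying and EQ-5D rows all have a 2-week entry. The GHSQ row does not, and neither does the row for use of health services and treatment. The secondary hypothesis applies 2 weeks to help-seeking along with the other outcomes.

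**The case against.** The strongest reply is that this is a drafting slip. The SDQ is an existing instrument cited in its Spanish version, and nothing says that forms will be scored from this summary sentence rather than from the instrument's own key. The mismatch between 24 items and a maximum of 50 itself suggests loose drafting. This stands as far as it goes: a reader might infer that symptoms will in fact be analysed backwards, and the document does not show that. It shows only that the printed rule and the printed interpretation cannot both be followed.

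Three further inferences are tempting and are not supported.
- *Healthy pupils would be flagged as at risk.* The cut-off sentence is a general remark about the instrument. *Statistical analysis* names no SDQ cut-off and describes no flagging procedure.
- *The SDQ total wrongly mixes prosocial behaviour with symptoms.* The inversion rule aligns positive items with the rest, and the article says that five subscale scores are produced. Nothing in it requires a total built from four subscales.
- *The 5 to 35 range proves that 'no one' is summed.* It does not, since five real sources with 'no one' left out give the same range. Unreversed inclusion is the plainer reading, because 'no one' is named among the rated options just before the sum and the article does state reversals for the CAMI and the SDQ. It is not the only reading. Even on it, the total keeps its direction overall; the spread shrinks from 30 to 18 points.

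It is also fair to say that both scales are listed among the other outcomes, not the primary ones.

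**Conclusion.** The point holds, with different certainty for its parts.
- **Certain from the text:** the SDQ coding contradicts the stated meaning of a high score; 24 items give a maximum of 48, not 50; and the 2-week help-seeking hypothesis has no GHSQ assessment in Table 3.
- **Conditional:** the GHSQ problem (29 and 11 in place of 35 and 5) assumes that 'no one' is one of the five summed ratings and is not reversed. If it is rated but left out, the total is sound and only the description is unclear.

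These are scoring rules and visits that the article chose to state, so this is an inconsistency and not detail left to an analysis plan. The consequence for the SDQ, a complete change of sign, follows only if the printed coding is applied literally. Mental health literacy, stigma, the primary analysis and the sample size are untouched.

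**What to change.** 1. **SDQ coding:** state that symptom items are coded not true = 0, somewhat true = 1, absolutely true = 2, with positive items reversed, so that a higher total means more difficulty.
2. **SDQ range:** make the item count and the range agree (24 items with 0 to 48, or 25 items with 0 to 50), according to the form actually used.
3. **GHSQ:** list the summed options and state that 'no one' is either reverse-scored or left out of the sum.
4. **Timing:** limit the help-seeking hypothesis to 6 and 12 months, or otherwise reconcile it with Table 3.

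The cost is a few sentences and a check of the scoring syntax, ideally before outcome data are analysed by arm. No new data are needed if the hypothesis is brought into line with Table 3; adding a 2-week GHSQ instead would mean one more administration.

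### The SDQ response labels are listed in an order that makes a higher total mean fewer problems, while the same paragraph treats a high score as risk

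*Protocol article*

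**What the plan says.** All of the scoring text is in one paragraph of the protocol article, under Mental health symptoms and emotional well-being.

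- Item coding: "Each item is rated 0, 1 or 2 points in accordance with being “absolutely true”, “somewhat true” or “not true".
- Reverse scoring: "The score is inverted in those items whose presence indicates positive features".
- Item count and range: "The SDQ consists of 24 items which generate scores along five subscales", and "The total score ranges from 0 to 50".
- Meaning of a high score: "individuals with scores above the cut-off (depending on each study population) should be evaluated more closely due to the increased risk". The paragraph closes by citing a reliability coefficient for the total difficulties scale.

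The outcome's standing is given elsewhere. Others outcomes says: "Other outcomes of the study are the mental health symptoms and emotional wellbeing". The secondary hypothesis in Background is directional: the interventions "will reduce mental health symptoms, increase emotional well-being and help-seeking behaviours". Table 3 lists the SDQ as the only instrument under mental health symptoms and emotional well-being, measured at baseline, 2 weeks, 6 months and 12 months. No other part of the article gives a different SDQ coding or direction.

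**The concern.** The coding rule and the interpretation rule point in opposite directions. A pupil for whom a symptom is absolutely true gets 0 on that item. Inverting the positive items does not repair this. It only brings the strengths into line with symptom items that already run from low (worse) to high (better). The total therefore rises with better mental health, yet the paragraph goes on to read a high total as risk.

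At stake is the direction of the symptom result under the secondary hypothesis. An analyst who programmed the coding sentence literally, and then interpreted the output as a difficulties score, would report a benefit as harm or harm as benefit. Checks of range, spread or internal consistency would not reveal it, because reflecting every item leaves all three unchanged. Only the mean would move, to the other end of the scale.

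**Working it through.** **Inputs**, all from the SDQ paragraph:
- Printed item code *c*: absolutely true = 0, somewhat true = 1, not true = 2 (labels matched to points in order).
- Positive items are inverted, so they contribute 2 − *c*. Problem items contribute *c*.
- Number of items *k* = 24, of which *p* are positive. The paragraph does not give *p*, so it is left free.

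**Stated range.** The maximum is 2*k* = 2 × 24 = 48, so the stated range of 0 to 50 is not reproduced. It would need 25 items (2 × 25 = 50). This is a separate discrepancy. The result on direction is the same for either count.

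**Direction as printed.** Total *T* = Σ(problem items) *c* + Σ(positive items) (2 − *c*).
- Most symptomatic pupil (every problem absolutely true, every strength not true): (24 − *p*) × 0 + *p* × (2 − 2) = 0.
- Healthiest pupil (every problem not true, every strength absolutely true): (24 − *p*) × 2 + *p* × (2 − 0) = 48.

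*p* cancels, so the result does not depend on how many items are positive. Evaluating it with 0, 5 and 10 positive items gave 0 and 48 each time (0 and 50 with 25 items).

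**Direction with the labels reversed.** Replace *c* by 2 − *c*, keeping the inversion of positive items:

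*T′* = Σ(problem items) (2 − *c*) + Σ(positive items) *c* = 48 − *T*.

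The most symptomatic pupil now scores 48 and the healthiest 0, which is the direction the cut-off sentence requires.

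**Effect on a comparison between arms.** Since *T* = 48 − *T′* for every pupil, mean(*T*, arm A) − mean(*T*, arm B) = −[mean(*T′*, arm A) − mean(*T′*, arm B)]. The constant drops out, the size is unchanged and the sign is opposite. As an illustration only, with simulated data for two groups of 85 pupils and 24 items, the difference was −2.26 with the labels reversed and +2.26 with the labels as printed.

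**The case against.** The strongest reply is that the intended direction is already clear. Two statements in the paragraph, on the cut-off and on the total difficulties scale, fix high as worse, and only the order of one list disagrees. The article names an existing, validated instrument in its Spanish version, so a transposed list in a condensed article is the likeliest explanation. The SDQ sentence also lacks the word *respectively*, which the authors use when they map labels to points for the RIBS and the EQ-5D-5L.

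Much of this stands. A transposition is plausible, and the mapping is natural rather than explicit. But the contradiction remains on the page. Reading labels and points in order is how the article's other scales work, and nothing else in the article tells the analyst which rule to follow.

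Three stronger readings are tempting, and the documents do not support them:
- *That the sign of the symptom result will be reversed.* This needs two further events: data scored in the printed order, and the result then read as high = worse. The article does not show what the scoring syntax does.
- *That risk reductions would count the healthiest pupils as cases.* Statistical analysis says only that relative and absolute risk reduction will be examined. It ties neither to the SDQ, and the SDQ paragraph gives no numerical cut-off and plans no dichotomy.
- *That the trial's main conclusion is at risk.* The primary outcomes are mental health literacy and stigma. The sample size, based on literacy scores, does not involve the SDQ.

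**Conclusion.** The inconsistency is real and can be shown from the one paragraph, without any outside scoring manual. Scored as printed, the total runs from 0 for the most symptomatic pupil to 48 for the healthiest, opposite to the interpretation given in the same place. The only assumption here is that labels and points are matched in the order listed.

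The consequence is conditional. If data are scored as printed and read as difficulties, the direction of this outcome is reversed in full. If the database already codes the labels the other way, the error is confined to the text. The article does not allow a reader to tell which applies. Because the outcome is not primary and the repair is small, the severity is moderate. It should still be settled before SDQ scores are computed, because the secondary hypothesis on symptoms is directional.

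**What to change.** Reverse the order of the three labels so that items score 0 for not true, 1 for somewhat true and 2 for absolutely true. Keep the existing inversion of items that describe positive features, and add that a higher total means more difficulties. Before any SDQ score is computed, check the coding in the data-import template (the Measures section describes import through a teleform program) and in the scoring syntax against this rule.

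The change should not alter which items or subscales enter the total. The mismatch between item count and range, and the presentation of the prosocial subscale on its own, are separate matters that this edit leaves alone.

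Cost: a correction to one sentence, one added statement of direction and one check of syntax. No new data are needed, and the design, sample size and primary analysis do not change.

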### Intentions to change

***States of Change Scale (SCS)*** (Spanish version). This is based on the Transtheoretical Change Model developed by James C. DiClemente O. Prochaska and Carlo [42, 43] to assess the degree of intention, disposition or attitude towards change. This instrument contains a total of five items which measure the process of evolutionary change in the following levels: (a) Precontemplation; (b) Contemplation; (c) Preparation for action; (d) Action; and e) Maintenance. The scale used is a Likert scale from 1 to 5 following the order of evolution of the items.

### Bullying and cyber-bullying behaviours

Four yes/no questions were specially developed for the purposes of this study to ask whether a person has been a victim or a perpetrator of a bullying and/or a cyberbullying incident.

### Health-related quality of life

The ***EuroQol 5D-5 L questionnaire (EQ-5D-5 L)*** [44, 45] is composed of two sections: the EQ-5D-5 L descriptive EQ system and the Visual Analogue Scale (EQ VAS). The descriptive system comprises five dimensions: mobility, self-care, usual activities, pain/discomfort, anxiety/depression; and each dimension has five levels: “no problems”, “slight problems”, “moderate problems”, “severe problems”, and “extreme problems”. The user response results in a 1-digit number expressing the level selected for that dimension in a Likert scale from 1 to 5, respectively. The EQ VAS records the respondent’s self-rated health on a visual analogue scale with endpoints labelled ‘the best health you can imagine’ that carries a value of 100, and ‘the worst health you can imagine’ that carries a value of 0.

